**Fig. 2 Fig2:**
[figure not shown]
Participating patients

### (Early) termination

For each participating patient, the study ends on 20 December 2021. Early study termination occurs if the patient withdraws from the study or stops dialysis treatment. Reasons to stop dialysis include kidney transplantation, recovery of kidney function, the wish to stop dialysis, or death.

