## Methods

### Study design

DOMESTICO is a nationwide, prospective, observational cohort study comparing home dialysis with ICHD. The maximum follow-up period of the study is 48 months. At present, 53 Dutch dialysis centres (covering 96% of Dutch centres) and 1 Belgian dialysis centre have agreed to recruit patients (Fig. 1). The study is conducted according to the principles of the Declaration of Helsinki and in accordance with the Medical Research Involving Human Subjects Act (WMO).

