#### Secondary outcome parameters

Secondary outcome parameters are hospitalisation, mortality, other clinical parameters, costs, and technique failure.

The cause of each hospitalisation episode will be categorised into the following categories (using ICD-10 codes) [47]:
Cardiac (including myocardial ischaemia/infarction, cardiac arrest/arrhythmia, cardiac failure, fluid overload/pulmonary edema, haemorrhagic pericarditis);Vascular disease (including pulmonary embolus, stroke, cerebrovascular haemorrhage, ruptured vascular aneurysm, mesenteric infarction, peripheral arterial disease);Infection, non-dialysis related (including bacteraemia/sepsis, cardiac infection, HIV, osteomyelitis, respiratory infection, urinary tract infection);Dialysis related (including dialysis access infection, peritonitis, PD catheter leakage/exchange/removal, fistula operation, renal fluid overload, bleeding);Malignancy;Bleeding, non-dialysis related (including intracranial bleeding, gastro-intestinal bleeding, other causes of bleeding);Other causes.

Mortality will be categorised into the following categories (using ERA-EDTA codes) [48]:
Sudden death ‘with unknown cause’;Cardiac (including myocardial ischaemia/infarction, cardiac arrest/arrhythmia, cardiac failure, fluid overload/pulmonary edema, haemorrhagic pericarditis);Vascular (including pulmonary embolus, stroke, cerebrovascular haemorrhage, ruptured vascular aneurysm, mesenteric infarction, peripheral arterial disease);Infectious, dialysis related (including dialysis access infection, peritonitis);Infectious, non-dialysis related (including bacteraemia/sepsis, cardiac infection, HIV, osteomyelitis, respiratory infection, urinary tract infection);Malignancy;Bleeding (including dialysis related bleeding, intracranial bleeding, gastro-intestinal bleeding, other causes of bleeding);Overall deterioration in clinical condition/stopping dialysis;Other causes.

Besides hospitalisation and mortality, several clinical parameters will be recorded including blood pressure and use of antihypertensive drugs, haemoglobin and use of erythropoiesis-stimulating agents, phosphate levels and use of phosphate binders, vascular access parameters, and nutritional status.

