### Data collection

All study outcomes, except the SeMaS, will be assessed at baseline, after 3 months, 6 months, and thereafter every 6 months until end of follow-up or end of the study (Table 2).

Data will be registered in case report forms (CRF). IBM Data Collection will be used as CRF. The database is developed by Nefrovisie and follows the principles of Good Clinical Practice (i.e. it has an audit trail, possibility for electronic signing, direct validation of inserted data, authorisation per form and user). Nefrovisie will also host the database for the duration of the study. The database will be archived for future research during 15 years after termination of the study.

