### Statistical analysis

All statistical analyses will be performed using statistical software such as SPSS and Stata. Univariable and multivariable regression analysis will be conducted. In case of repeated measures, multilevel analysis or generalised estimating equations will be applied. Possible confounders determined a priori are age, gender, marital status, level of education, work status, cause of renal failure, prior RRT with dialysis vintage, comorbidities, albumin, body mass index, and protein energy wasting. Cumulative incidence of hospitalisation, mortality, and technique failure will be reported in Kaplan Meier curves. In case of missing data, multiple imputation techniques will be used to impute the missing values where appropriate.

Overall costs will be compared across the treatment groups and 95% confidence intervals will be estimated using bootstrapping techniques. The cost-effectiveness of different dialysis modalities will be determined using a state transition model. This model captures the changes in treatment modality, including transplantation, over time. The results of the DOMESTICO study will be used as input parameters for this model.

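### Read as written, the termination rule puts deaths after a patient chooses to stop dialysis outside follow-up, which conflicts with the mortality categories and makes censoring in the mortality curves informative

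*Protocol article*

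**What the plan says.** The Protocol article, section *(Early) termination*, sets a common closing date ("For each participating patient, the study ends on 20 December 2021") and an individual exit rule: "Early study termination occurs if the patient withdraws from the study or stops dialysis treatment". It then explains: "Reasons to stop dialysis include kidney transplantation, recovery of kidney function, the wish to stop dialysis, or death". The wish to stop and death are thus two separate exits.

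Section *Data collection* schedules assessments at baseline, 3 and 6 months, and "thereafter every 6 months until end of follow-up or end of the study". No contact or vital-status check after an early exit is described.

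Three other parts of the article bear on this:

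- *Secondary outcome parameters* makes mortality an outcome, and one cause-of-death category is "Overall deterioration in clinical condition/stopping dialysis".
- The same section defines technique failure of home dialysis as death or transfer to in-centre haemodialysis, with 30-day and 180-day versions. Permanent technique failure also counts cessation of dialysis. Transplantation is reported separately.
- *Statistical analysis* plans Kaplan-Meier curves for mortality and technique failure. It also plans a state transition model for cost-effectiveness: "This model captures the changes in treatment modality, including transplantation, over time". On its inputs it says: "The results of the DOMESTICO study will be used as input parameters for this model".

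**The concern.** Under the termination rule, a patient who decides to stop dialysis leaves the study at that decision. If the rule is followed literally, the death that follows is not a study event and the patient enters the mortality curve as censored alive. The mortality categories, however, make room for exactly this kind of death, so the two sections do not fit together.

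The statistical problem is the censoring. Kaplan-Meier treats a censored patient as having the same future risk as those who remain. A dialysis-dependent patient who has just chosen to stop does not have that risk. The consequences would be:

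- mortality understated;
- the death component of the 30-day and 180-day technique-failure composites understated, because a home patient who stops and then dies is neither a recorded death nor a transfer;
- survival overstated, and QALYs with it, since QALYs combine utilities with survival;
- a possible bias between modalities if the share of patients who stop differs between home and in-centre dialysis. This matters for the stated hypothesis of at least comparable clinical outcomes. The listed confounders cannot restore deaths that were never recorded.

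**Working it through.** **Setting the rules side by side**

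| Situation of a home dialysis patient | Exit under *(Early) termination* | Recorded as death? | 30/180-day technique failure? | Permanent technique failure? |
|---|---|---|---|---|
| Dies on dialysis | Death | Yes | Yes | Yes |
| Chooses to stop, then dies | At cessation | No, read literally | No, read literally | Yes, at cessation |
| Transplanted | At transplantation | Not applicable at exit | No, reported separately | No, reported separately |

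The second row is the conflict. Permanent technique failure is protected because cessation is itself an event there.

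**Illustrating the size**

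Inputs:

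- Five-year survival of 45%, from *Background*.
- A constant hazard (assumption).
- s, the share of deaths that follow elective cessation (assumption; the documents give no figure). The range is 0% to 30%, where 0% stands for full capture of such deaths.
- The interval from cessation to death is short, and s is constant over time (assumptions).

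Step 1, yearly hazard: h = −ln(0.45)/5 = 0.1597. Check: exp(−5 × 0.1597) = 0.45, the article's figure.

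Step 2, 12-month mortality with all deaths seen: 1 − exp(−0.1597) = 14.8%.

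Step 3, recorded 12-month mortality when a share s is censored at cessation: 1 − exp(−h(1 − s)).

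| s | h(1 − s) | Recorded mortality | Shortfall (percentage points) |
|---|---|---|---|
| 0% | 0.1597 | 14.8% | 0 |
| 10% | 0.1437 | 13.4% | 1.4 |
| 20% | 0.1278 | 12.0% | 2.8 |
| 30% | 0.1118 | 10.6% | 4.2 |

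Step 4, effect on the comparison. If true mortality is equal in the two groups and the shares are s1 and s2, the apparent hazard ratio is (1 − s1)/(1 − s2):

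- equal shares: 1.00;
- 10% against 20%: 0.90/0.80 = 1.125;
- 10% against 30%: 0.90/0.70 = 1.29.

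The group in which more patients stop would look better. The documents do not say which group that is.

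**Sample size.** The article's figures are unaffected. The standard two-sample formula gives 175 per group for the SF-12 (difference 3, SD 10) and 698 for the EQ-5D-5L (difference 0.03, SD 0.20), against the stated 175 and 700.

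**The case against.** The strongest reply is that the loss of these deaths is inferred from silence. The article says when participation ends. It nowhere says that vital status goes uncollected afterwards. The category for stopping dialysis suggests that such deaths are meant to be recorded, and listing death as a reason to stop dialysis shows that the termination section is loosely worded. Checks at exit are also a detail that a full protocol, not shown here, may contain. This stands to the extent that nobody can say the deaths *are* lost, which is why the range above includes 0%. It does not remove the point: the rule is stated, and it conflicts with another section. If capture is intended, the termination section states the rule wrongly.

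It is also fair to object that the 10% to 30% shares have no source in the documents and that no difference between groups has been shown. Both are true. The figures illustrate; they do not estimate.

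A reader might go further and infer three things that the documents do not support:

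- *That QALYs are understated.* Missed deaths work the other way: survival looks longer, and QALYs rise with it.
- *That all technique-failure results are affected.* Permanent technique failure counts cessation as an event.
- *That the transition model cannot be filled for transplantation.* Transplantation is a recorded exit and is reported separately, so the rate of entry to that state is observed. Only utilities, costs and survival after transplantation fall outside follow-up. The article does not say that the study supplies those, or that it is the model's only source; unit costs already come from an external manual.

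**Conclusion.** The concern holds for deaths after elective cessation, with the termination rule read as written. That rule conflicts with the cause-of-death categories and would make censoring informative in the planned mortality curves. The direction is clear: mortality and the 30-day and 180-day technique-failure composites too low, survival and QALYs too high. The size is unknown. Under a constant hazard, 14.8% mortality at 12 months would be recorded as 13.4% to 10.6% for assumed shares of 10% to 30%, and would be unchanged if these deaths are in practice captured. Bias between modalities arises only if cessation rates differ, which the documents do not tell us.

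This affects secondary outcomes, not the sample size. It is worth correcting because the rule is explicit and the remedy cheap. On transplantation, only a wording note remains.

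**What to change.** Reconcile *(Early) termination*, *Secondary outcome parameters* and *Statistical analysis* as follows:

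1. Separate the end of questionnaires from the end of vital-status follow-up. Questionnaires may still end when dialysis ends.
2. For every patient who has not withdrawn consent, obtain vital status, with date and cause of any death, up to 20 December 2021.
3. State that deaths after elective cessation count as deaths in the mortality analysis, and say how they enter the 30-day and 180-day technique-failure composites.
4. Name the source of utilities, costs and survival after transplantation in the transition model.

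This concerns data collection and analysis only. It takes no position on when dialysis should be stopped.

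The cost is a short amendment and one vital-status check per terminated patient, with a little chart work at the centres. Item 4 costs one sentence if external inputs are used. The article reports 338 of 1600 planned patients included (338/1600 = 21%), so most of the cohort could be covered from the start. The end-of-study check could also reach those who have already left, within the consent they gave.

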### Outcomes

#### Primary outcome parameter

The primary outcome parameter is the patient’s HRQoL, a PRO, determined with the 12-item Short Form (SF-12) health survey and the Dialysis Symptom Index (DSI) [39, 40]. These questionnaires were carefully selected as Patient Reported Outcome Measures (PROMs) in nephrological care by the Dutch Kidney Patients Association, the Dutch Federation for Nephrology, Nefrovisie (the Dutch Quality Institute for Nephrology), and Leiden University Medical Center [41, 42].

The SF-12 is the shorter version of the Short Form-36 (SF-36), one of the most widely used surveys to assess HRQoL [43, 44]. The SF-36 consists of eight domains: Physical functioning, Role-physical, Bodily pain, General health, Vitality, Social function, Role-emotional and Mental health. These domains are summarised in the Physical Component Summary (PCS) score and the Mental Component Summary (MCS) score. In the SF-12 these summary scores are calculated from the 12 most important questions (explaining ~ 90% variance) of the SF-36 questionnaire [39, 45]. As the average difference in summary scores between SF-36 and SF-12 is quite small, for time-efficiency reasons, the SF-12 can be used reliably in cohort studies [46].

The DSI consists of 30 questions evaluating the severity of symptoms relevant to dialysis and ESRD patients (Table 1). Patients report the level of burden of specific symptoms on a 5-point Likert scale, options range from ‘not at all bothersome’ to ‘very bothersome’ [40].

**Table 1 Tab1:** Items Dialysis Symptom Index

1. Constipation	16. Chest pain
2. Nausea	17. Headache
3. Vomiting	18. Muscle soreness
4. Diarrhoea	19. Difficulty concentrating
5. Decreased appetite	20. Dry skin
6. Muscle cramps	21. Itching
7. Swelling in legs	22. Worrying
8. Shortness of breath	23. Feeling nervous
9. Lightheadedness or dizziness	24. Trouble falling asleep
10. Restless legs or difficulty keeping legs still	25. Trouble staying asleep
11. Numbness or tingling in feet	26. Feeling irritable
12. Feeling tired or lack of energy	27. Feeling sad
13. Cough	28. Feeling anxious
14. Dry mouth	29. Decreased interest in sex
15. Bone or joint pain	30. Difficulty becoming sexually aroused

#### Secondary outcome parameters

Secondary outcome parameters are hospitalisation, mortality, other clinical parameters, costs, and technique failure.

The cause of each hospitalisation episode will be categorised into the following categories (using ICD-10 codes) [47]:
Cardiac (including myocardial ischaemia/infarction, cardiac arrest/arrhythmia, cardiac failure, fluid overload/pulmonary edema, haemorrhagic pericarditis);Vascular disease (including pulmonary embolus, stroke, cerebrovascular haemorrhage, ruptured vascular aneurysm, mesenteric infarction, peripheral arterial disease);Infection, non-dialysis related (including bacteraemia/sepsis, cardiac infection, HIV, osteomyelitis, respiratory infection, urinary tract infection);Dialysis related (including dialysis access infection, peritonitis, PD catheter leakage/exchange/removal, fistula operation, renal fluid overload, bleeding);Malignancy;Bleeding, non-dialysis related (including intracranial bleeding, gastro-intestinal bleeding, other causes of bleeding);Other causes.

Mortality will be categorised into the following categories (using ERA-EDTA codes) [48]:
Sudden death ‘with unknown cause’;Cardiac (including myocardial ischaemia/infarction, cardiac arrest/arrhythmia, cardiac failure, fluid overload/pulmonary edema, haemorrhagic pericarditis);Vascular (including pulmonary embolus, stroke, cerebrovascular haemorrhage, ruptured vascular aneurysm, mesenteric infarction, peripheral arterial disease);Infectious, dialysis related (including dialysis access infection, peritonitis);Infectious, non-dialysis related (including bacteraemia/sepsis, cardiac infection, HIV, osteomyelitis, respiratory infection, urinary tract infection);Malignancy;Bleeding (including dialysis related bleeding, intracranial bleeding, gastro-intestinal bleeding, other causes of bleeding);Overall deterioration in clinical condition/stopping dialysis;Other causes.

Besides hospitalisation and mortality, several clinical parameters will be recorded including blood pressure and use of antihypertensive drugs, haemoglobin and use of erythropoiesis-stimulating agents, phosphate levels and use of phosphate binders, vascular access parameters, and nutritional status.

Direct healthcare costs, patient costs, and costs with regard to productivity losses will be assessed with a subset of questions from the Institute for Medical Technology Assessment (iMTA) Productivity Cost Questionnaire (iPCQ) and the iMTA Medical Cost Questionnaire (iMCQ) [49, 50]. To capture all health care costs for the population under research a small number of disease specific services are added to the standard iMCQ, e.g. home dialysis. Given the fact that many patients need substantial help from close relatives, also use of informal care by patients will be assessed. The costs related to the healthcare consumption, the dialysis procedures, the diagnostic tests and (over-the-counter) medication will be derived from the patient’s medical chart during the study. Unit costs will be derived from the Dutch manual for costing studies [51].

To further examine cost-effectiveness, the EuroQol-5D-5L (EQ5D-5L) questionnaire will be used. The EQ-5D-5L measures HRQoL on the following 5 domains: mobility, self-care, usual activities, pain/discomfort, and anxiety/depression. Each domain has 5 levels of functioning, ranging from ‘no problems’ to ‘extreme problems’. The EQ-5D-5L also contains a visual analogue scale on which the current health state can be indicated. The EQ-5D scores can be used to calculate utilities, which describe HRQoL on a scale from 0 (dead) to 1 (perfect health). Utilities can be combined with survival to calculate quality adjusted life years (QALYs). As outcome measure for cost-effectiveness, the costs per additional QALY will be analysed [52, 53].

All participating patients will also receive a self-management screening questionnaire (SeMaS) at baseline, in order to investigate whether self-management can predict a successful home dialysis treatment. This questionnaire shows the abilities and possible barriers for self-management by asking questions about the burden of disease, locus of control, self-efficacy, social support, coping style, anxiety, depression, and skills [54, 55].

Table 2 provides an overview of the moments when participating patients will fill in the aforementioned questionnaires.

**Table 2 Tab2:** Overview questionnaires

Visit	SF-12 and DSI	iPCQ and iMCQ	EQ-5D-5L	SeMaS
Baseline	X	X	X	X
At 3 and 6 months	X	X	X	
At 9 months and every 6 months thereafter		X		
At 12 months and every 6 months thereafter	X	X	X	

*SF-12* Short Form-12, *DSI* Dialysis Symptom Index, *iPCQ* Institute for Medical Technology Assessment (iMTA) Productivity Cost Questionnaire, *iMCQ* iMTA Medical Cost Questionnaire, *SeMaS* self-management screening questionnaire

Finally, technique failure rate of home dialysis, defined by a composite outcome of death or transfer to ICHD, will be assessed. Both a 30-days and a 180-days definition of technique failure will be used according to the minimum number of days the patient received ICHD after cessation of home dialysis [56]. Permanent technique failure is defined by death or transfer to ICHD (using the 180-days definition), or cessation of dialysis. Death-censored technique failure will be reported separately. Transfer to kidney transplantation is not considered to be technique failure and will also be reported separately [56].

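### As worded, permanent technique failure counts recovery of kidney function as a failure of home dialysis, because only transplantation is exempted

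*Protocol article*

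**What the plan says.** The protocol article, under Secondary outcome parameters, gives technique failure in layers.

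- Base definition: "technique failure rate of home dialysis, defined by a composite outcome of death or transfer to ICHD, will be assessed".
- Confirmation windows: "Both a 30-days and a 180-days definition of technique failure will be used according to the minimum number of days the patient received ICHD".
- Permanent variant: "Permanent technique failure is defined by death or transfer to ICHD (using the 180-days definition), or cessation of dialysis".
- Exemption: "Transfer to kidney transplantation is not considered to be technique failure and will also be reported separately". Failure with deaths censored is also to be reported on its own.

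The section (Early) termination says when participation ends: "Early study termination occurs if the patient withdraws from the study or stops dialysis treatment". It then explains the second trigger: "Reasons to stop dialysis include kidney transplantation, recovery of kidney function, the wish to stop dialysis, or death".

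**The concern.** The permanent variant adds a third component, cessation, with no reason attached. One favourable way of leaving dialysis, transplantation, is then taken out by name. The other favourable way that the article itself names, recovery of kidney function, is not. An analyst who follows the text would code a recovered patient as a permanent failure of home dialysis.

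That is a good outcome counted as a bad one. It raises the permanent failure proportion by the number of recoveries. It also leaves the layers inconsistent: a recovered patient is a permanent technique failure without being a technique failure. The Discussion section says that the clinical results are meant to support shared decision-making, so a figure labelled permanent failure should not contain patients who no longer need dialysis.

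**Working it through.** **Step 1. Set the texts side by side.** The article states no rate, event count or power for technique failure, so there is no figure to reproduce. The check starts from the wording. Each reason for stopping dialysis listed under (Early) termination is taken through the definitions under Secondary outcome parameters.

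| Reason dialysis stops | Base definition (death or transfer to ICHD) | Permanent variant as written |
|---|---|---|
| Death | failure | failure |
| Patient's wish to stop | not in itself a failure | failure, through cessation |
| Kidney transplantation | not a failure | not a failure, exempted by name |
| Recovery of kidney function | not a failure | failure, through cessation; no exemption |

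Only the last row gives a result that the authors are unlikely to intend.

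**Step 2. Size, under assumed rates.** None of these inputs is in the article; all are assumptions, per patient-year on home dialysis and constant over time:

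- transfer to ICHD 0.20 (every transfer taken to satisfy the 180-day rule)
- death 0.16
- transplantation 0.10
- recovery r = 0.01 (low) or 0.05 (high)

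Failure hazard without recovery: 0.20 + 0.16 = 0.36.
Total exit hazard: T = 0.36 + 0.10 + r.

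With competing exits, two-year cumulative incidence is (failure hazard / T) × (1 − exp(−2T)).

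*r = 0.01:* T = 0.47, and 1 − exp(−0.94) = 0.6094.
- Recovery counted: (0.37 / 0.47) × 0.6094 = 0.480
- Recovery not counted: (0.36 / 0.47) × 0.6094 = 0.467
- Difference: (0.01 / 0.47) × 0.6094 = 0.013, or 1.3 points
- Recoveries as a share of counted failures: 0.01 / 0.37 = 2.7%

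*r = 0.05:* T = 0.51, and 1 − exp(−1.02) = 0.6394.
- Recovery counted: (0.41 / 0.51) × 0.6394 = 0.514
- Recovery not counted: (0.36 / 0.51) × 0.6394 = 0.451
- Difference: (0.05 / 0.51) × 0.6394 = 0.063, or 6.3 points
- Recoveries as a share of counted failures: 0.05 / 0.41 = 12.2%

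**Step 3. Does the scale matter?** The Statistical analysis section plans Kaplan-Meier curves. On that scale, with all non-failure exits censored, the two-year figure is 1 − exp(−2 × failure hazard).

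- Recovery censored: 1 − exp(−0.72) = 0.513
- Recovery counted, r = 0.01: 1 − exp(−0.74) = 0.523, a difference of 1.0 point
- Recovery counted, r = 0.05: 1 − exp(−0.82) = 0.560, a difference of 4.6 points

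The size is somewhat smaller, the direction the same.

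**The case against.** The best defence is that cessation here means withdrawal from treatment. It stands next to death in the definition, and the mortality categories in the same section pair stopping dialysis with overall deterioration. The list of reasons for stopping belongs to the rules for ending study participation; it does not define the endpoint, and the technique failure paragraph does not refer to it. The paragraph also cites a source for its definitions, which may settle how recovery is handled.

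Part of this stands. The link between the two sections is an inference, and the narrow reading is possible. But nothing in the technique failure paragraph limits the word to withdrawal, and the express exemption of transplantation suggests that the authors saw a need to name favourable exits. The list is also the article's only account of why dialysis stops, and it names recovery.

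It is also fair that the size rests wholly on assumed rates, and that at the low end it is about one point on one variant of a secondary outcome.

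A reader might go further and infer that the 180-day rule fails for late transfers, since "For each participating patient, the study ends on 20 December 2021" and a transfer after 23 June 2021 cannot complete 180 observed days. The date arithmetic is right, but the article does not say that such transfers are scored as non-failures. They can be censored, or the risk period can be closed early. A death within the window still counts through the death component. Handling of unconfirmed transfers at study close is commonly left to the full protocol or analysis plan, which are not shown. This is not an error in the article.

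**Conclusion.** The point holds in a limited form. The permanent variant, taken as written together with the listed reasons for stopping dialysis, scores recovery of kidney function as a permanent failure of home dialysis. Under the assumed rates the two-year figure is too high by about 1.3 to 6.3 percentage points (3% to 12% of counted failures). This range depends on constant rates that the article does not give, and on every transfer meeting the 180-day rule.

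Three broader readings are not supported:

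- It is not true that every kind of cessation counts, because transplantation is exempted.
- Technique failure as a whole is not misstated. Cessation is not part of the 30-day or 180-day outcomes, and the primary quality-of-life outcome and the sample size are untouched.
- The cost-effectiveness result cannot be said to be wrong for this reason. The article says that study results feed a state transition model, but not that this composite is one of the inputs.

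The correction is worth making because the rule is stated, gives a wrong classification when followed, and is easy to repair.

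**What to change.** Reconcile the technique failure definition with the list of reasons under (Early) termination. Word the third component of the permanent variant as *cessation of dialysis for reasons other than kidney transplantation or recovery of kidney function*. Add that recovery is reported separately, as is already planned for transplantation. If withdrawal was all that was meant, this wording makes that explicit.

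The cost is one clause and one short reporting statement. No new data should be needed, provided that the reason for stopping dialysis is recorded when participation ends early. The 30-day and 180-day definitions stay as they are.
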